##### Secondary outcome 3: tolerance

Outcome 3 is the score after the last tDCS session in the following tolerance measures:tDCS-AEQ (adverse effects questionnaire) [42]VAMS (visual analog mood scale) [43].

##### Secondary outcome 4: response markers and predictors

Outcome 4a is the differences at baseline in the following EAP measures between patients with cognitive improvement and patients without cognitive improvement after active tDCS:Correlations (*z*-scores) between left prefrontal and temporal cortical areas (i.e., areas stimulated with tDCS) measured with resting-state functional magnetic resonance imaging (MRI).Spectral power (dB) and inter-assay coherence (%) in gamma frequency (40-Hz) during specific auditory paradigms (auditory steady-state, oddball, tone-matching) measured with electroencephalography (EEG).GABA and glutamate levels (mM) within left prefrontal and temporal cortical areas measured with resting-state Magnetic Resonance Spectroscopy (MRS)radiotracer binding potential on GABA-A receptors (Binding Potential) within left prefrontal and temporal cortical areas measured with resting-state [^11^C]flumazenil positron emission tomography MRI (PET-MRI).

Outcome 4b is the changes between baseline and 1-month follow-up in the same EAP measures in patients with cognitive improvement compared to patients without cognitive improvement after active tDCS.

### Participant timeline {13}

The participant timeline is detailed in Fig. 2 (SPIRIT figure).

### Sample size {14}

Based on previous tDCS studies in patients with schizophrenia (rev. in [17], we assume that a third (33%) of participants in the active tDCS group and 5% of participants in the sham tDCS group will be responders (improvement greater than or equal to *Z*=0.5 from baseline on the MCCB total score). Based on this estimated difference, we calculated that 60 patients are required to demonstrate a difference between the two groups with a power of 80% (*p* = 0.05).

### Recruitment {15}

We developed a multicenter study with four centers in France to achieve sufficient recruitment. Participants with recent-onset schizophrenia will be recruited in each study center with the help of local early-intervention psychiatric teams that specialize in the early stages of schizophrenia. Potential participants will be approached at their regular clinic consultations by investigators with the study information leaflet. All the investigators have already proven their abilities to achieve noninvasive brain stimulation studies (including tDCS) in patients with schizophrenia as highlighted by several international publications. All the investigators are active members or have been trained by members of the French association for the use of noninvasive brain stimulation in psychiatry (see https://www.afpbn.org/sections/step). Annual joint meetings between investigators are scheduled, and periodical newsletters will be sent to all the investigators and research members involved in the study to inform about updates and important points. In case of recruitment issues, new study centers will be open.

### Concealment mechanism {16b}

For the trial (30 active, 30 sham), randomization will be conducted using the online IWRS system. The randomization will take place on the day of the first tDCS session in order to avoid the allocation of a sequence that will not be used and to ensure allocation concealment.

### Implementation {16c}

Participants who fulfill the inclusion criteria and give consent will be enrolled by study investigators. Participants will be assigned a unique anonymous identification code by an investigator. This code is composed of the number of the study center number, the participant’s initials (first letter of the name, first letter of the surname), and the last number from 1 to 60. The code will be notified in an electronic Case Report Form (eCRF). Participants will be randomized by an investigator using the online IWRS system, resulting in random 1:1 allocation into one of the 2 study arms (*N*=30 active tDCS and *N*=30 sham tDCS). The IWRS system will provide a 5-digit number code that will be notified at inclusion in the eCRF. The code will be digitally entered into the tDCS device to deliver either to active or sham tDCS.

## Assignment of interventions: blinding

### Who will be blinded {17a}

Blinding will be maintained at 3 levels: participants, research staff members including investigators, and data analysts. If different from the investigator, care providers will be also blinded to the intervention. Blinding for the tDCS condition will be achieved for the research staff members who will administer the tDCS by the use of a randomization code (see details in §16c) and for the participants by ensuring identical appearance and sensation for both active and sham conditions (see details in §6b). The duration of the intervention will be 20 min in both active and sham sessions. Outcome assessments, imaging, and biological data will be collected and analyzed by research staff members blind to group assignment and different from the staff member who will administer the tDCS.

### Procedure for unblinding if needed {17b}

Unblinding will be permissible under the following circumstances during the trial period: appearance of non-inclusion criteria, withdraw of consent to participate in the study, worsening of the clinical condition observed by the investigator justifying the discontinuation of the protocol, and serious adverse effects. Participant’s allocated intervention will be revealed to the subject by the investigator who enrolled the participant.

## Data collection and management

### Plans for assessment and collection of outcomes {18a}

Primary outcome will be assessed by trained neuropsychologists and other outcomes will be assessed by neuropsychologists, psychiatrists, and members of the research staff. All participating investigators and other research staff members that will collect outcomes have been trained for the described assessments. Study subjects will be informed that they can take breaks between tests. Of note, outcomes including neuropsychological tests and clinical and tolerance measurements are frequently used in tDCS and schizophrenia studies. All study sites are experts in those two clinical and research fields. Regarding neurobiological outcomes, all three centers routinely perform electrophysiological and brain imaging examinations. They regularly participate in multicenter trials for which a convergence of acquisition conditions is required. They regularly collaborate with local specialist engineers and manufacturing engineers.

#### Positive and Negative Syndrome Scale (PANSS)

The PANSS is a 30-item clinician-rated scale of the main clinical symptoms observed in schizophrenia. The items are rated on a Likert-type scale, ranking from no symptom (1) to highest intensity (7) of the symptom. The PANSS evaluates the intensity of symptoms based on 3 categories (7 positive items, 7 negative items, and 16 general psychopathology items) or 5 dimensions positive, negative, disorganization, depression, grandiosity/excitement. The PANSS is validated in the French language and has a good consistency and inter-judge reliability (coefficients > 0.60) [32, 45].

#### Auditory Hallucinations Rating Scale (AHRS)

The AHRS is a 7-item clinician-rated scale that generates a detailed description of auditory hallucinations severity for the last 24-h time period. The items are rated on Likert-type scales, ranking from no feature (0) to highest intensity (5, 6, 7, or 9 depending on the individual item) of the auditory hallucination feature. The measured features are frequency, vividness, loudness, length (single words, sentences, phrases, or extended discourse), attentional salience, degree of distress associated with auditory hallucinations, and the number of distinct speaking voices. The AHRS-related “Hallucination Change Scale” (HCS) can be used as outcomes to assess changes from baseline to follow-up in auditory hallucinations severity. The AHRS is validated in the French language and has good test-retest reliability and inter-judge reliability (coefficients > 0.60) [33, 46].

#### Brief Negative Symptom Scale (BNSS)

The BNSS is a 13-item clinician-rated scale specifically developed to measure negative symptoms in participants with schizophrenia for the last week period. The items are rated on a Likert-type scale, ranking from no alteration (0) to highest alteration (6). The measured negative symptom dimensions are blunted affect, alogia, asociality, anhedonia, avolition and associated distress. The BNSS is validated in the French language and has a very good consistency and inter-judge reliability (coefficients > 0.80) [34, 38].

#### Calgary Depression Scale for Schizophrenia (CDSS)

The CDSS is a 9-item clinician-rated scale specifically developed to measure depression symptoms in participants with schizophrenia for the last 2-weeks period. The items are rated on a Likert-type scale, ranking from no symptom (0) to highest intensity (3). The CDSS is validated in the French language and has a good consistency and inter-judge reliability (coefficients > 0.60) [30, 47].

#### Clinical Global Impression (CGI)

The CGI is a brief 3-item clinician-rated scale that involves the assessment of the severity of the disorder at baseline (item 1), the assessment of overall improvement at follow-up (item 2), and the measurement of the therapeutic index which assesses the clinical efficacy and associated side effects (item 3) [35, 48].

#### Beck Cognitive Insight Scale (BCIS)

The BCIS is a 15-item self-questionnaire developed to measure depression cognitive insight in patients with schizophrenia and early stages of psychosis. Each item is rated by the participant on a 4-point Likert scale ranging from 0 (“do not agree at all”) to 3 (“agree completely”). Two cognitive domains are measured: “self-reflectiveness”, which represents the ability to re-evaluate unusual experiences and correct erroneous inference, and “self-certainty,” which evaluates one’s tendency to be overconfident about one's own judgments. The BCIS is validated in the French language and has good internal consistency (coefficients > 0.60) [36, 49, 50].

#### Cardiff Anomalous Perceptions Scale (CAPS)

The CAPS is a 32-item self-rated questionnaire developed to perceptual anomalies in participants with schizophrenia. Each item is presented as a question requiring an answer of “yes” or “no”. The measured perceptual anomalies are Schneiderian first-rank symptoms, temporal lobe experiences, and chemosensations. The CAPS is validated in the French language and has satisfactory psychometric parameters [37, 51].

#### Self-evaluation of Negative Symptoms (SNS)

The SNS is a 20-item self-rated questionnaire specifically developed to assess the subjective experience of negative symptoms of schizophrenia for the last week period. The participant puts a cross in the box next to the response that best corresponds to her/his current feelings based on the previous week, scoring 0 (strongly disagree), 1 (somewhat agree), or 2 (strongly agree). The SNS is validated in the French language and has a good consistency (coefficients > 0.60) and satisfactory acceptance by participants [38].

#### Subjective Scale To Investigate Cognition in Schizophrenia (SSTICS)

The SSTICS is a 21-item self-rated scale that assesses the participant’s subjective experiences of cognitive impairment as indicated from objective tests. The scale consists of 21 Likert-type questions set in the context of everyday activities and situations. The participant puts a cross in the box next to the response that best corresponds to her/his recent feelings, scoring from 0 (never) to 4 (very often). The SSTICS is validated in the French language and has a good consistency (coefficients > 0.60), stability over time, and correlations with objective measures of cognitive abilities [39].

#### Questionnaire of the Functional Remission Observatory Group in Schizophrenia (FROGS)

The FROGS is a 19-item clinical-rated scale that measures the core aspects of functional remission in schizophrenia based on 3 factors (social functioning, daily life, and treatment). The items are rated on a Likert-type scale ranking from does not (1) to does completely (5). The FROGS is validated in the French language [40].

#### Schizophrenia Quality of Life Questionnaire Short Form (S-QoL 18)

The S-QoL18 scale is 18-item self-rated questionnaire measuring eight dimensions of quality of life: psychological wellbeing, self-esteem, family relationships, relationships with friends, resilience, physical well-being, autonomy, and sentimental life. The participant puts a cross in the box next to the response that best corresponds to her/his recent feelings on a 5-point Likert scale. The S-QoL 18 is validated in the French language and has satisfactory psychometric to evaluate the quality of life in participants with schizophrenia [41].

#### tDCS adverse effects questionnaire (tDCS-AEQ)

The tDCS-AEQ is the most frequently used questionnaire to measure the most reported side effects of tDCS (headaches, neck pain, mood alterations, and seizures, rated by the participant on a scale of 0 to 5) [42].

### Neurobiological outcomes measures

#### Electroencephalography

EEG recordings will be carried out using a 64-electrode EEG (BrainVision actiCHamp THE amplifier). Participants will be comfortably seated in a chair in a quiet room. An appropriately sized EEG cap will be placed on the subject’s scalp and a conductive gel will be applied between the scalp and each electrode. At the end of the examination, the electrodes and the EEG cap are removed and the participants will be offered to wash their hair by providing shampoo and towels. The EEG examination lasts approximately 2 h including set-up and breaks. The following auditory tasks will be performed by the participant during the EEG recording:

Auditory Steady-State task (ASSR) will be played through a headset (Sennheiser HD 558) placed on the EEG cap. The ASSR stimuli consist of sound “clicks” of 1 ms duration and 80 dB intensity, broadcast in 500 ms sequences at a frequency of 20Hz, 30Hz, or 40Hz. Three series of 200 stimuli will be broadcast for each frequency [52].

Tone-matching Task (TMT) will be played through the same headset. This computerized task consists in presenting to subjects pairs of non-verbal short basic “beeps” tones (300 ms) with a brief silent interval between tones of each pair (500 ms). Within each pair, tones are either identical or differ in a basic feature (e.g., frequency, length, intensity) by specified amounts. Participants have to respond by pressing “same” or “different” on a 2-button press [8, 53].

Auditory oddball task will consist of sequences of tones presented in random order during a passive (block 1) and an active (block 2) listening condition. Standard stimuli (70% sequential probability) will be harmonic tones composed of three superimposed sinusoids (500, 1000, and 1500 Hz) ~ 80 dB, 100ms in duration with 5-ms rise and fall time. Frequency, intensity, and duration deviants (10% probability each) will be 10% lower in frequency, 10 dB lower in intensity and 50 ms longer in duration respectively. At the beginning of each run, the first 15 auditory stimuli are standards. During passive listening, participants had to simply listen to the tones. During active listening they had to attend and press a key in response to the deviant tones. Passive will elicit an N1 component and mismatch negativity (MMN). Active listening will elicit a P3 component [54, 55].

#### Magnetic resonance imaging

MRI resting-state acquisitions will be carried out using 3-Tesla MRI Scanners. Participants will be positioned on a special table that slides into the MRI. To avoid head movements during the examination, head restraints will be used. The subject will wear a headset designed to attenuate magnet noise while allowing to communicate with the experimenter and notify wish to interrupt the examination at any moment. During all the MRI acquisitions, the subject will be asked to relax, to look at a cross on a screen and not to think about anything. After installation of the participant in the MRI scan, a laser light will be aligned on the orbito-meatal line. This alignment will be regularly checked and corrected if necessary. The MRI examination lasts approximately 2 h including set-up and breaks. The following acquisitions will be carried out:aMRI: A few minutes of anatomical MRI sequence (T1-weighted 3D MP-RAGE) will be used for spatial normalization in stereotactic space, anatomical segmentation and parcellation, and extraction of time activity curves by regions during the next acquisitions. Cerebral areas of each participant will be mapped by deformations of standard atlases on the T1 image of the subject.rsfMRI: A 15-min resting-state functional MRI sequence will be acquired in axial multislice using traditional gradient echo sequences with a maximum temporal resolution of 3 s. The acquisition will be used to establish maps of the activation and functional connectivity of the fronto-temporal cortical network. A short acquisition to characterize the local inhomogeneities of the B0 magnetic field will be included in order to correct the geometrical distortions they induce.MRS: A 30-min acquisition of monovoxel magnetic resonance spectroscopy with GABA editing will be carried out. Two large voxels of interest (left prefrontal and temporal cortices, dimension 3×3×3 cm3 each) will be targeted based on T1 anatomical images. The acquisition will be performed by a "MEGA-PRESS" MRI sequence, which simultaneously removes the water signal and captures the spectral resonance of GABA (γ-CH2, 3 ppm) to estimate its relative concentration (mM) to a stable reference peak. Parameters will be the following: TR/TE = 2000/68 (ms), water signal suppression, 320 excitations divided into 80 dynamics with editing pulse alternately applied at 7.46 and 1.90 ppm between dynamics, phase cycling on 8 excitations per dynamic. Spectra without water signal suppression will also be acquired as a reference for pre-processing.PET-MRI: A positron emission tomography acquisition with the GABA marker ([^11^C]flumazenil) will be carried out simultaneously to the MRI sequences described above (PET-MRI). A preliminary interview with a nuclear physician will be performed on the day of the PET-MRI examination. The PET scanner, associated with the MRI imager, is a Biograph mMR, Siemens Healthcare, with an internal tunnel diameter of 60 cm and a useful field of view of 50×50×50 cm^2^ in MRI and 59×59×26 cm^2^ in PET. The PET images produced are volumes of 127 slices of 2mm thickness. The spatial resolution (NEMA standard) is 4.3 mm (total width at half height, FWHM) and isotropic at the center of the field of view. The combination of PET and MRI scans will, after coregistration, improve the spatial resolution and thus refine the data analysis. PET acquisition is performed simultaneously with the MRI sequences described above. PET-MRI requires the installation of a venous catheter by a medical electroradiology manipulator. In our protocol, carbon-11-labeled flumazenil will be synthesized only once per participant. After MRI tracking and attenuation correction sequences have been performed, the injection of the [^11^C]flumazenil 2.5 MBq/kg bolus will be performed at the same time as the start of the PET recording. Dynamic PET data will be recorded 60 min after the injection of [^11^C]flumazenil. Of note, only one of the investigation centers (Centre Hospitalier Le Vinatier) has a PET-MRI device and will thus participate in the PET-MRI acquisition.

### Plans to promote participant retention and complete follow-up {18b}

To promote participant retention, participants will earn 200€ after completing all visits of the trial. To minimize missed study visits and loss to follow-up, all participant visits will be scheduled by a member of the research staff reminded to the participants by phone calls or text messages the day before. The importance of being present at each visit will me reminded to the participant. In case of missed visit, the investigator will seek a new appointment with the participant.

### Data management {19}

In each study site, clinical research assistants will conduct the local study monitoring, which includes appointment management, data recording, and storage in the secured eCRF. A paper version of the CRF will be used to ensure direct ratings during visits and to collect self-questionnaires. Clinical research assistants will continually check the quality of the data, compare the data to medical records and contact the outcome assessors in case of missing or aberrant data. A statement by which all clinicians of the research staff will have direct access to medical records is included in the consent form. Of note, these professionals are bound by strict confidentiality rules and are not allowed to disclose any personal identity or medical information. At specific time points, the quality department of the study sponsor will independently check the consent forms and eCRF for data abnormalities according to standard ranges and, in such cases, inform the investigator. The informed consent form will include a statement by which the patients allow the sponsor’s duly authorized personnel (trial monitoring team) to have direct access to original medical records which supports data on the eCRF (e.g., patient’s medical file, appointment books, and original laboratory records).

### Confidentiality {27}

Both CRF (electronic and paper versions) will be declared to the CNIL (French National Commission for Data Protection and Liberties). Paper CRFs will be kept in locked files at the study sites for 15 years. In all study-related documents, participants will appear only in the form of an ID code (see §16c for details) to ensure confidentiality. All members of the research staff who will have direct access to the data before, during, and after the trial will be bound to strict confidentiality rules and will not be allowed to disclose personal or medical information.

## Statistical methods

### Statistical analysis plan

In general, the normality of the data distributions will be investigated with Shapiro-Wilk tests. Between-group comparisons will be performed with Mann-Whitney *z*-tests and two-sample *t*-tests for non-normal and normal continuous outcomes, respectively. Categorical data will be compared with chi-square tests. Both intention-to-treat and per-protocol analyses will be conducted. In case of significant interactions, post hoc analyses will be conducted using appropriate contrasts. Analyses will be adjusted or stratified by the study site as part of a sensitivity analysis. The significance threshold will be set at *P*-value < 0.05 and appropriate effect sizes of significant results will be calculated.

### Statistical methods for primary and secondary outcomes {20a}

#### Main outcome

The percentage of “responders” showing an improvement in global cognitive improvement (increase ≥ 0.5 of the global MCCB *Z*-score at 1-month follow-up) will be compared between the active tDCS group (*N*=30) and the sham tDCS group (*N*=30) using a chi-square test. In addition, a binomial test will be used to test the superiority of the proportion of responders to active tDCS vs. sham tDCS.

#### Secondary outcomes

##### Secondary outcome 2: clinical efficacy

Outcome 2a: the percentage of “responders” and the number of responders at 3-month follow-up will be compared using the same tests as for the main outcome.Outcomes 2b: the changes from baseline to endpoints in MCCB cognitive domains subscores will be analyzed using mixed effects regression models with group (active or sham) and time (before tDCS, 1-month follow-up, 3-month follow-up) as independent variables.Outcomes 2c: the changes from baseline to endpoints in clinical symptom measures will be analyzed using mixed effects regression models with group (active or sham) and time (before tDCS, after tDCS, 1-month follow-up, 3-month follow-up) as independent variables.Outcomes 2d: the changes from baseline to endpoints in schizophrenia outcome will be analyzed using mixed effects regression models with group (active or sham) and time (before tDCS, 1-month follow-up, 3-month follow-up) as independent variables.

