#### Secondary outcome

##### Secondary outcome 2: clinical efficacy

Outcome 2a will be the number of responders at 3 months.

Outcome 2b will be the changes from baseline to 1-month and 3-month endpoints in each MCCB domains subscores (processing speed, attention/vigilance, working memory, verbal learning, visual learning, problem-solving, emotional awareness) and total score. To avoid learning effects, the MCCB will use different sets of parallel tests with the same difficulty levels at 1 month and 3 months.

Outcome 2c will be the changes from baseline to after tDCS and 1-month and 3-month endpoints in the following symptom measures:Schizophrenia symptoms will be assessed using the PANSS (Positive and Negative Syndrome Scale) total score. In addition, PANSS subscores for positive, negative, disorganization, depression, and grandiosity/excitement symptoms will be used as outcomes [32].Auditory hallucinations, one of the key symptoms of schizophrenia, will be assessed using the AHRS (Auditory Hallucination Rating Scale) [33].Negative symptoms will be additionally assessed using the Brief Negative Symptom Scale (BNSS) [34].Depressive symptoms will be assessed using the Calgary Depression Scale for Schizophrenia (CDSS) total score [30].Global symptom severity and treatment response will be assessed using the Clinical Global Impressions Scale (CGI) total score [35].Cognitive insight abilities will be assessed using the Beck Cognitive Insight Scale total score [36].Perceptual anomalies will be assessed using the self-rated Cardiff Anomalous Perceptions Scale (CAPS) total score [37].Subjective experience of negative symptoms will be assessed using the self-rated Self-evaluation of Negative Symptoms (SNS) total score [38].Subjective experiences of cognitive impairment will be assessed using the self-rated Subjective Scale To Investigate Cognition in Schizophrenia (SSTICS) total score [39].

Outcome 2d will be the changes from baseline to 1-month and 3-month endpoints in the following general outcome measures:Functional outcome will be assessed using the FROGS (Functional Remission Observatory Group in Schizophrenia) total score [40]Quality of life will be assessed by the Schizophrenia Quality of Life Questionnaire Short Form (S-QoL 18) total score [41]

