### Methods for additional analyses (e.g., subgroup analyses) {20b}

Subgroup analyses will be performed regarding possible confounders such as the study site. In case of baseline differences between the 2 groups (active tDCS and sham tDCS), statistical analyses will be adjusted to take into account specific variables that may have influenced the results (e.g., antipsychotic dosage, illness duration, and age).

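### Outcomes 2b–2d: the mixed-model wording mixes change scores with a pre-treatment time level, names neither the group-by-time effect nor baseline as covariate, and so gives up precision

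*Protocol article*

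**What the plan says.** Under Statistical methods for primary and secondary outcomes {20a}, the Protocol article says of outcome 2b that "the changes from baseline to endpoints in MCCB cognitive domains subscores will be analyzed using mixed effects regression models". Its list of predictors for that outcome has two factors, and the visit before treatment is one of the levels of the second: "with group (active or sham) and time (before tDCS, 1-month follow-up, 3-month follow-up) as independent variables". Outcome 2d has the same factor list. Outcome 2c has four time levels: "group (active or sham) and time (before tDCS, after tDCS, 1-month follow-up, 3-month follow-up) as independent variables". The Outcomes {12} section also defines these endpoints as changes, for example "Outcome 2b will be the changes from baseline to 1-month and 3-month endpoints in each MCCB domains subscores".

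Two other sections bear on the models. The general Statistical analysis plan section says: "In case of significant interactions, post hoc analyses will be conducted using appropriate contrasts". Methods for additional analyses {20b} says: "In case of baseline differences between the 2 groups (active tDCS and sham tDCS), statistical analyses will be adjusted". Its examples of adjustment variables are antipsychotic dosage, illness duration and age. The baseline value of the outcome is not among them.

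**The concern.** Response and time factor do not fit together as written. If the response is change from baseline, the pre-treatment level is zero for every patient and carries no information. If the response is the raw score, that level belongs in the model, but the treatment effect is then the group-by-time term, which the outcome descriptions do not name. Two analysts could fit different models from the same sentences.

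Two further choices have a cost even on the most favourable reading. First, the baseline score is collected on everyone but is not a pre-specified covariate; adjustment depends on seeing a baseline difference. Second, Objectives {7} asks for comparisons at named visits, whereas the general methods offer contrasts only after a significant interaction. At stake are the precision and completeness of the reported effects for the MCCB domains and for every symptom, functioning and quality-of-life scale.

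**Working it through.** **The plan's own figure.** The only design calculation is for the primary responder comparison. Sample size {14} assumes "a third (33%) of participants in the active tDCS group and 5% of participants in the sham tDCS group will be responders", with 80% power and p = 0.05 (two-sided assumed). With pooled variance and no continuity correction, the mean proportion is 0.19 and

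n = [1.96·√(2·0.19·0.81) + 0.842·√(0.33·0.67 + 0.05·0.95)]² / 0.28² = (1.087 + 0.436)² / 0.0784 ≈ 29.6,

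so 30 per arm and 60 in total. The figure reproduces, and nothing below touches it.

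**Inputs for 2b–2d.** n = 30 per arm and the number of visits K (3 for 2b and 2d, 4 for 2c) come from the protocol. It gives no SD, effect or between-visit correlation for these outcomes. I assume SD = 1, a difference δ = 0.5 at every post-treatment visit, equal correlation ρ between visits (0.5, 0.7, 0.9), complete data and two-sided 5% tests.

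**Step 1: one-visit contrast.** Both versions below estimate the full δ.

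- Group-by-time contrast against the pre-treatment visit: SE = √(4(1−ρ)/n)
- Adjusted for baseline (or common baseline mean): SE = √(2(1−ρ²)/n)

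| ρ | SE, unadjusted | SE, adjusted | Power, unadjusted | Power, adjusted |
|---|---|---|---|---|
| 0.5 | 0.258 | 0.224 | 49% | 61% |
| 0.7 | 0.200 | 0.184 | 71% | 77% |
| 0.9 | 0.115 | 0.113 | 99% | 99% |

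The SE ratio is √((1+ρ)/2): 0.87, 0.92 and 0.97.

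**Step 2: the interaction gate.** The overall group-by-time test has noncentrality nδ²(K−1)/(2K(1−ρ)). For K = 3 and ρ = 0.5 this is 30·0.25·2/(2·3·0.5) = 5.0. With an F test on 2 and 116 degrees of freedom, power is about 49% at ρ = 0.5 and 72% at ρ = 0.7 (noncentrality 8.3), and above 99% at ρ = 0.9 (noncentrality 25). With a true 0.5 SD effect, the visit contrasts would go unreported in about 51%, 28% and under 1% of trials. Four visits give nearly the same (48%, 72%, above 99% power).

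**Step 3: what the group main effect would estimate.** Averaging over K visits, one of them before treatment, gives δ(K−1)/K: 0.333 for K = 3 (two thirds of δ) and 0.375 for K = 4 (three quarters).

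- *Raw scores:* SE = √(2(1+(K−1)ρ)/(Kn)). For K = 3 this is 0.211, 0.231 and 0.249, and power is 35%, 30% and 27%.
- *Change scores with the zero row:* estimate and SE shrink by the same factor. At ρ = 0.7 and K = 3, z = 0.333/0.115 = 2.89, the same as 0.500/0.173 = 2.89 for the average post-treatment change.

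**Step 4: what the protocol says about correlation.** Most quoted coefficients are internal-consistency or inter-judge figures. Only the MCCB total score (above 0.90) and the AHRS (above 0.60) have one attached to test-retest reliability, and the 2b model is described for MCCB domain subscores. The range for ρ is therefore an assumption.

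**The case against.** The strongest reply is that the outcome descriptions list factors in shorthand. The general methods foresee interactions, and in 2b–2d group-by-time is the only candidate. The stated hypothesis, greater improvement from baseline under active stimulation, is itself a group-by-time question. On that reading the pre-treatment level is needed, the response is the raw score, and the estimate is unbiased under randomisation. Full term lists and the reported contrast are also commonly left to an analysis plan, which is not shown. Baseline already enters such a model as a response, so omitting it as a covariate costs efficiency and is not an error.

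Most of this stands. In particular, a reader might infer that the stated model dilutes the treatment effect to two thirds or three quarters and cuts power to about 30%. The document does not support that. Step 3 applies only if an analyst reports the group main effect, and the protocol never names that as the test. On the change-score reading the estimate is mis-scaled, but the balanced-data test statistic is not weakened.

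Three things are not answered. The response and the time levels still conflict as written. The stated rule makes contrasts conditional on a significant interaction. Adjustment is triggered by observed imbalance instead of being fixed in advance. These are statements on the page, not details left to another document.

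**Conclusion.** The point holds as an ambiguity with a modest, avoidable loss of precision, confined to secondary outcomes 2b–2d. On the natural group-by-time reading there is no bias and no dilution. Pre-specified baseline adjustment would cut the one-visit SE by about 13% at ρ = 0.5, 8% at ρ = 0.7 and 2–3% at ρ = 0.9. The power gain is about 12 points, 6–7 points and nil.

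The interaction gate could suppress the visit-specific results in roughly half of trials at ρ = 0.5 and over a quarter at ρ = 0.7, despite a real effect. Since many of those contrasts would not reach significance themselves, what is lost is mainly the estimate and its interval.

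All of this rests on the assumed 0.5 SD constant effect, equal correlations and complete data. The primary chi-square comparison and N = 60 are unaffected.

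**What to change.** For 2b–2d, state that the post-treatment scores are modelled with the baseline score as a pre-specified covariate and with group, visit and group-by-visit as terms. Alternatively, keep the pre-treatment visit as a response and constrain the arms to a common baseline mean; in balanced data this gives the same precision, and the pre-treatment time level may then stay.

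Name the group contrast at 1 month and at 3 months (and at the end of tDCS for 2c) as the reported effect. Give it with a 95% CI whether or not the overall interaction is significant. With many scales reported this way, present the contrasts as estimates, not as a series of confirmatory tests.

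The cost is rewording the three outcome sentences and qualifying the general sentence on post hoc contrasts. Data, visits, software and sample size do not change.
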